### Assessment

Adolescents and parents will complete questionnaires administered electronically at pre-treatment (T1), mid-treatment (T2), post- treatment (T3) and 12-month follow-up (T4) (see Table 2 and Additional file 1: Figure S1 (the SPIRIT table)). We plan for the group leaders to meet with the adolescents at all points of data collection (T1-T4) to secure outcome data from as many as possible, regardless of participation or discontinuation in the intervention.

**Table 2 Tab2:** Overview of measures

Measure	Scale (informant)	T1	T2	T3	T4
Primary outcome measures					
Anxiety symptoms	SCAS (c/p)	●	●	●	●
Interference of anxiety symptoms	CALIS (c/p)	●	●	●	●
Secondary outcome measures					
Depression	SMFQ (c/p)	●		●	●
Quality of life	KINDL (c/p)	●		●	●
General mental health	SDQ (c/p)	●		●	●
Clinical Global Impression	CGI (g)	●		●	●
Other measures					
Age, gender, socioeconomic status, ethnicity	From the youth@hordaland-survey (c/p)	●			
Medication, service use, school absenteeism	Developed for this study (p)	●		●	●
Youth Engagement in and between sessions^*^	YES (c/g)				
Sleep problems	From the youth@hordaland-survey (c)	●		●	●
Children’s Automatic Thought Scale	CATS (c)	●	●	●	●
General Self-Efficacy Scale	GSE	●	●	●	
Family cohesion	READ subscale (c)	●			
Social support	READ subscale (c)	●			
Adverse childhood experiences	From the youth@hordaland-survey (c)	●			
Parenting psychopathology/stress	DASS (p)	●			
Group leader preference	Developed for this study (g)	●			
Caregiver strain	CGSQ (p)	●		●	●
Life events	LE (c)				●
Client Satisfaction Scale	CSS (c/p)			●	
Treatment Credibility and Expectancy Scale	(CES-c/p)**				

T1 = Baseline/pre-intervention, T2 = mid-intervention/at 4 weeks, T3 = post intervention/at 10 weeks, T4 = 1-year follow-up. c = child, p = parent, g = group leader

^*^Administered to group leaders after every session and to youths in session 3-9 (CHILLED) and session3-5 (VAAG)

^**^Administered to adolescents after session one and to parents after first parent session

*SCAS* Spence Children’s Anxiety Scale*, CALIS* Children Anxiety Life Interference Scale, *CGI* Clinical Global Impression Scale, *SMFQ* Short Mood and Feeling Questionnaire, *KINDL* Kinder Lebensqualität Fragebogen, *SDQ* Strength and Difficulties Questionnaire, *CATS* Children’s Automatic Thought Scale, *GSE* General Self-Efficacy Scale, *YES* Youth Engagement in and between Sessions, *CEQ* Credibility and Expectancy Questionnaire, *READ* Resilience Scale for Adolescents, *DASS* Depression, Anxiety and Stress Scale, *CGSQ* Caregiver Strain Questionnaire; the *youth@hordaland-survey* = a population-based survey administered by Uni Research Health, *CSS* Client Satisfaction Scale

#### Primary outcome measures

*Spence Children’s Anxiety Scale*-child and parent version (SCAS-c/p) [36, 44] is a questionnaire designed to assess youth anxiety symptoms. Both child and parent versions contain 38 items (in addition, the child version has six positive filler items). SCAS c/p consists of six 4-point subscales for specific anxiety areas: panic/agoraphobia, social phobia, generalized anxiety, separation anxiety, obsessive compulsive, and specific phobias. Each subscale can be scored separately as well as added together for an overall anxiety symptom score. SCAS c/p has been found to have good psychometric properties [36, 44–46].

*Child Anxiety Life Interference Scale*-child and parent version (CALIS-c/p) [37] assesses life interference and impairment from youth anxiety in the areas of home, social life, school and activities. In addition to a nine-item scale filled out separately by adolescents and caregivers, caregivers also rate how the child’s anxiety interferes with their own life (seven items; e.g., career, relationship with spouse). Each item is rated on a 5-point scale. CALIS has demonstrated satisfactory psychometric properties [37].

#### Secondary outcome measures

*Short Moods & Feelings Questionnaire*-child and parent version (SMFQ-c/p) [47] is a 13-item scale assessing youth depressive symptoms within the last 2 weeks. Items are rated on a 3-point scale from “not true” to “true.” The SMFQ-c/p is designed for children and adolescents aged 8-16 years. The scale has shown good psychometric properties [47–49].

The *Clinical Global Impression scale* (CGI) [50] is a measure of global functioning covering the overall severity of symptoms (CGI Severity; CGI-S) and changes in functioning over time (CGI Improvement; CGI-I). CGI-S/I is scored on a 7-point scale. In the present study, CGI-S/I will be completed by the school nurses (pre- and post-treatment). Ratings will be based on a joint semi-structured interview with caregivers and adolescents. All interviews will be videotaped, and reliability will be checked by external observers rating about 15% of the interviews.

*Strengths and Difficulties Questionnaire*-child and parent version (SDQ-c/p) [51] is a 25-item behavioral screening questionnaire assessing emotional problems, conduct problems, hyperactivity-inattention, peer problems and prosocial behaviors in children and teenagers. Items are scored on a 3-point scale. SDQ-c/p also includes a five-item scale on functional impairment scored on a 4-point scale. SDQ-c/p has demonstrated good psychometric properties [52, 53].

*Questionnaire for Measuring Health-Related Quality of Life in Children and Adolescents, The Revised Version-child and parent version *(KINDLRc/p) [54] measures quality of life. KINDL-R-c/p consists of six subscales with four items each (physical and emotional well-being, self-esteem, family, friends and school), all items scored on a 5-point scale. The German versions of KINDL-R-c/p have satisfactory psychometric properties [54], with the Norwegian translated version evaluated as promising [55, 56].

#### Other measures

Further measures are included to allow for descriptive information about the participants as well as analyses of moderators and mediators. *Socio-demographic information* comprises gender, age, ethnicity, parents’ education and family economy, as well as the use of health services, medication and school absenteeism. *Sleep problems* covers sleep duration, difficulties initiating and maintaining sleep, and tiredness/sleepiness, all derived from the youth@hordaland-survey [57, 58]. The *General Self-Efficacy Scale* (GSE) [59] assesses optimistic self-beliefs, whereas the *Children’s Automatic Thoughts Scale* (CATS) [60] assesses negative thoughts associated with mental health problems in youths. The *Treatment Credibility and Expectancy Scale* (CES-c/p) [61] refers to how believable, convincing and logical a treatment is perceived to be, while treatment expectancies refer to the improvements believed to be achieved. The *Client Satisfaction Scale* (CSS-c/p) assesses both parents’ and adolescents’ evaluation of the program. *Youth Engagement in and between Sessions* (YES) assesses the adolescents’ participation in in-session exercises and discussions and exposure training between sessions. *Adverse life experiences* cover the occurrence of serious accidents such as violence or unwanted sexual acts and bullying, previously applied in the youth@hordaland-survey [62]. A *Life-event Scale* (LE) comprises positive (e.g., sporting achievement), negative (e.g., family member becomes ill) and neutral events (e.g., change school) and is completed by the adolescents at 1-year follow-up. The *Resilience Scale* (READ) [63] measures the ability to handle stress and negative experiences. In the current study the subscales “Social resources” and “Family Cohesion” are included. The *Depression Anxiety Stress Scale* (DASS-21) [64] is a self-reported measure assessing parental symptoms of anxiety, stress and depression. The *Caregiver Strain Questionnaire* (CGSQ) [65] measures the negative impact on parents of caring for a child with emotional or behavioral problems. Finally, after completing the initial training group, leaders rate which of the two programs they prefer.

### Program implementation

#### Training and supervision of group leaders

Two group leaders will run each group, with one group leader and one co-leader. The main group leaders (*n* = 18) will be school nurses (with the exception of two mental health workers from primary health services). The co-leaders will be school nurses (*n* = 11), community psychologists (*n* = 3) and mental health workers from community mental health outpatient clinics (*n* = 5). At the start of the study the group leaders receive a 4-day skills-training workshop comprising basic CBT principles for youth anxiety, introduction to VAAG and CHILLED and training in how to conduct the pre-post assessment interviews. Additional training is given regularly during the inclusion period, with two 2-day workshops (i.e., on youth anxiety, recruiting participants, exposure training, cognitive restructuring and group processes).

#### Strategies to improve and measure adherence and competence

Supervision will be provided throughout the study. All sessions will be videotaped, and group leaders will receive feedback based on videotapes of sessions and according to a detailed supervision plan. The supervision plan entails information on the duration, structure, number and content of the supervision sessions. Supervision varies between 3 and 4.5 h for VAAG and 6 and 10.5 h for CHILLED per group depending on the number of groups the group leaders have administered. The supervisors are experienced CBT therapists, with a background in clinical child psychology, community psychology or child psychiatry. Decisions about discontinuing or modifying the interventions (e.g., referral to specialist treatment) will be discussed with the supervisor in each individual case. Videotaping the sessions allows for ratings of adherence and competence in the delivery of the programs. Between 20 and 40% of the videotaped sessions will be rated according to a scale for rating adherence and competence [66]. The scale has adequate psychometric properties and has previously been used in a CBT treatment study for anxious youth [67]. The scale assesses CBT structure, process and relational skills as well as specific goals for each session. School nurses volunteer for the study and do not receive extra pay, but receive free training and supervision. Some of the school nurses will be relieved from other duties to participate in the current study (about 20% less workload).

### Statistical analyses

#### Power calculation

Power calculations for differences among the three conditions, taking into account two repeated measurements with an assumed correlation of 0.6, yielded a required total sample size (power = 0.80, alpha = 0.05) of 294 children to obtain an effect size (ES) of 0.40. With an assumed attrition of 10%, we need to recruit 323 participants. Even though an average effect size in targeted prevention studies is 0.32 [26], we expect a somewhat larger effect size compared to WLC since we have included an intervention that has shown moderate to large effect sizes in previous studies when delivered as treatment or as a targeted preventive school intervention [31–33].

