## Methods

### Study design

This is a RCT with groups of 5-8 adolescents (12-16 years) allocated to two school-based CBT interventions and a control condition: (1) a brief intervention developed for the present study (VAAG), (2) a longer, more established intervention (CHILLED) and (3) a delayed access waitlist control group (WLC). Participants allocated to the two active interventions will start after a group of 5-8 adolescents has been assembled and randomized. Both interventions last for 10 weeks, VAAG comprises five sessions and CHILLED ten sessions. In addition CHILLED has two separate parent sessions. The expected number of hours of face-to-face professional contact is 18 h for the Chilled program and 5.5 h for VAAG. The waitlist group will be randomized in groups of 5-8 adolescents. Those allocated to the waitlist group will be randomized a second time to either VAAG or CHILLED after a delay of 10 weeks. Based on previous research, CBT early intervention for anxious youths is expected to be efficacious [26, 27]; therefore, we consider it unethical to withhold the intervention for adolescents allocated to the waitlist group for an extended period. Participants from all three conditions will be invited to a 1-year follow-up assessment. The overall study design is illustrated in Fig. 1, whereas the stages of the enrollment, interventions and assessments can be seen in Additional file 1: Figure S1 (The SPIRIT table).

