#### Enrollment and randomization

Eligible adolescents first meet with the school nurse for information about the study. This is followed by a semi-structured interview developed for this study, conducted with the adolescent and caregiver(s). The interview includes assessments of anxiety symptoms, severity and impairment, what goals the adolescent wants to achieve with regard to anxiety as well as assessment of whether exclusion criteria apply. Next, the adolescent and caregiver(s) complete a battery of questionnaires administered electronically. These may be completed either at the office of the school nurse or at home. Based on their score on the anxiety symptom measure and the interference measure, the adolescent is enrolled in the study. Randomization to condition occurs after having enrolled five to eight adolescents from the specific school, with the group serving as the unit of randomization. As 3 of the 18 schools are too small to recruit groups, youths from these three schools are included in groups at a nearby school, resulting in 15 sites for randomization. The randomization is done according to an outline prepared at the start of the study, using a computer-generated random digit procedure, comprising lists of six possibilities (2 CHILLED × 2 VAAG × 2 WLCs) at each school. After the waiting period the WLC group is randomized to CHILLED or VAAG. The randomization will be administered by staff employed at Uni Research Health. To reduce systematic biases between schools and group leaders, all three conditions will take place at each school, with group leaders being trained to deliver both CHILLED and VAAG.

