#### Data analytical plan

Data will be collected electronically. The effects of the two active interventions compared to the WLC will be analyzed by mixed effect models. The predictive value of the various pre-treatment characteristics will be evaluated using regression analyses. The test for non-inferiority will be performed for the primary outcome variables, followed by superiority analyses, including both primary and secondary outcome measures. Analysis will be performed according to an intention-to-treat procedure. Missing data will be handled by multiple imputations. Further details about the protocol are reported in the SPIRIT checklist (Additional file 2: Table S1).

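### The stated 0.80 power takes no account of the group as unit of randomisation; it should be restated over a range of within-group correlations

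*Protocol article*

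**What the plan says.** Under Enrollment and randomization, the protocol article states: "Randomization to condition occurs after having enrolled five to eight adolescents from the specific school, with the group serving as the unit of randomization". Under Study design, the active arms start once such a group has been assembled and randomised, and the same holds for the control arm: "The waitlist group will be randomized in groups of 5-8 adolescents". Each randomisation list holds two groups per condition at each school, across 15 sites, so allocation is 1:1:1 and every condition is meant to run at every site.

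Under Power calculation, the basis is given as "Power calculations for differences among the three conditions, taking into account two repeated measurements with an assumed correlation of 0.6", and this "yielded a required total sample size (power = 0.80, alpha = 0.05) of 294 children to obtain an effect size (ES) of 0.40". Then: "With an assumed attrition of 10%, we need to recruit 323 participants". That section gives no within-group correlation, group size or design effect, and no other section of the article supplies one.

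Under Data analytical plan: "The effects of the two active interventions compared to the WLC will be analyzed by mixed effect models". The random effects are not named.

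**The concern.** When whole groups are allocated, members of a group tend to resemble one another. They come from the same school or neighbouring schools and, in the active arms, share sessions and two leaders. Each extra member then adds less information than an independent participant would. A sample size that counts adolescents as independent overstates the power of such a design unless the within-group correlation is zero.

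The article publishes a complete calculation with a definite result, and that result does not reflect the unit of randomisation given a few sections earlier. This goes beyond condensed reporting: a later analysis plan can settle the model, but it cannot make the published basis for 0.80 correct. At stake is whether a reader can rely on the stated chance of detecting a 0.40 SD effect against waitlist.

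**Working it through.** **Inputs from the article.** Effect size 0.40 SD, alpha 0.05, power 0.80, three conditions, two measurements with correlation 0.6, equal allocation, groups of 5 to 8 (midpoint 6.5). Sidedness is not stated; a two-sided or omnibus test is assumed. The ICC is not given and is varied from 0.01 to 0.10.

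**Step 1: reproduce 294.**

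- Repeated-measures between-groups F test. With an outer difference of 0.40 and the third mean midway (0, 0.2, 0.4), f = 0.40 × √(1/6) = 0.163. The noncentrality is f² × N × 2/(1 + 0.6) = 0.02667 × 294 × 1.25 = 9.8, which gives power 0.803. The smallest multiple of three that reaches 0.80 is 294.
- Plain two-sample formula as a check: 2 × (1.96 + 0.842)² / 0.40² = 98.1 per arm, and 3 × 98.1 = 294.

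Both treat adolescents as independent (design effect 1). The first uses every stated input.

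**Step 2: add the clustering.** Design effect DE = 1 + (m − 1) × ICC, with m = 6.5. Power is recomputed at 294/DE, and the N that would keep 0.80 is 294 × DE.

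| ICC | DE | Effective N | Power at 294 (F test / pairwise) | N analysed for 0.80 |
|---|---|---|---|---|
| 0.01 | 1.055 | 279 | 0.78 / 0.78 | 311 |
| 0.02 | 1.11 | 265 | 0.76 / 0.76 | 327 |
| 0.05 | 1.275 | 231 | 0.69 / 0.70 | 375 |
| 0.10 | 1.55 | 190 | 0.60 / 0.61 | 456 |

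At ICC 0.002, DE = 1.011 and the F-test power is 0.798, so the calculation has practically no slack. Over group sizes 5 to 8 and ICC 0.01 to 0.10, power at 294 runs from about 0.79 down to 0.56.

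**Step 3: clustering in one of the two compared arms.** Waitlist groups are not treated together before the 10-week comparison. If only the active arm is correlated, the variance of the difference is proportional to (1 + DE)/98. At ICC 0.05 this is 2.275/98, and pairwise power is about 0.75.

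**Step 4: a more efficient analysis.** Baseline adjustment multiplies the variance by 1 − 0.6² = 0.64. Pairwise power at 98 per arm is then about 0.87 at ICC 0.05 and 0.80 at ICC 0.10.

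**Step 5: conditional error rates.** If the model left the randomised group out, the two-sided type I error would be 2 × [1 − Φ(1.96/√DE)]: 5.6%, 8.3% and 11.5% at ICC 0.01, 0.05 and 0.10. The one-sided 0.025 non-inferiority test would run at half of these, about 2.8%, 4.1% and 5.8%.

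**Degrees of freedom.** 294 participants form roughly 37 groups (of 8) to 59 groups (of 5). Even at ICC 0, using group-level degrees of freedom in the Step 1 calculation lowers power to about 0.76 to 0.78. The table does not include this.

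**The case against.** **The shortfall depends on how 294 was built.** The F-test reconstruction puts one active arm at half the effect, whereas the article expects both programmes to work and sets a non-inferiority margin of 0.1 SD between them. With means 0, 0.4 and 0.4 and the same variance factor (2 × (1 − 0.6) = 0.8), 222 participants would give 0.80. Power at 294 would then be about 0.89, 0.87, 0.82 and 0.73 at ICC 0.01, 0.02, 0.05 and 0.10. Pooling the active arms against waitlist gives about 0.89 at ICC 0.05 and 0.83 at 0.10. This stands as a limit on the size of the loss. It does not rescue the published figure, because those scenarios do not yield 294 from the stated inputs.

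**An allowance might be hidden in 294.** A baseline-adjusted pairwise calculation needs 63 per arm, and 63 × 1.55 = 97.7, which also rounds to 98 per arm. The coincidence is real, so the unclustered reading is strictly an inference. It is much the likelier one: the article lists what was taken into account, mentions no ICC, and 294 follows directly from that list.

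**School variance is largely controlled.** All three conditions are meant to run at each site, so between-school variance can be removed if school is in the model. What remains is correlation of groups within a school, which may be small. This stands; it is not shown to be zero.

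**A stronger reading is tempting.** A reader might infer that the trial's tests will be anti-conservative and non-inferiority too easily claimed. The article does not support that. It plans mixed models without naming the random effects, a mixed model is a natural place for a group term, and an analysis plan not shown here may specify one.

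**Conclusion.** The stated 0.80 is not justified as written. The group is the unit of randomisation in all three arms, the calculation behind 294 shows no allowance for it, and on that calculation any ICC above about 0.002 puts power below 0.80. At a mean group size of 6.5 the loss is modest at ICC 0.01 to 0.02 (about 0.78 to 0.76) and material at 0.05 to 0.10 (about 0.70 to 0.60). It is smaller if only one compared arm is clustered.

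The direction is firm. The size rests on an assumed ICC and on the reconstructed calculation. A reader might conclude that the trial cannot reach 80% power. That does not follow, since a baseline-adjusted model could keep about 0.80 up to ICC 0.10. The error-rate figures in Step 5 describe only what would happen if group were omitted from the model, which the article neither states nor excludes.

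**What to change.** 1. In the power section, replace the unqualified 0.80 with the power for 294 analysed participants under a design effect of 1 + (m − 1) × ICC, over a declared ICC range and group sizes of 5 to 8. Say which analysis the figure rests on (omnibus repeated-measures test, pairwise contrast or baseline-adjusted model), because the answer depends on it.
2. State that the efficacy, non-inferiority and imputation models include the randomised group, as a random intercept with small-sample degrees of freedom in the analysis models, and that school is accounted for. If the analysis plan already says so, a cross-reference is enough.

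No extra recruitment is called for: the article reports 310 adolescents already randomised by November 2016, with inclusion to close the following month. The cost is a few sentences, one model term and a less favourable stated power.

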**Methods/design:**

The present study is a randomized controlled trial comparing two CBT interventions to a waitlist control group. A total of 18 schools participate and we aim to recruit 323 adolescents (12-16 years). Youth who score above a cutoff on an anxiety symptom scale will be included in the study. School nurses recruit participants and deliver the interventions, with mental health workers as co-therapists and/or supervisors. Primary outcomes are level of anxiety symptoms and anxiety-related functional impairments. Secondary outcomes are level of depressive symptoms, quality of life and general psychosocial functioning. Non-inferiority between the two active interventions will be declared if a difference of 1.4 or less is found on the anxiety symptom measure post-intervention and a difference of 0.8 on the interference scale. Effects will be analyzed by mixed effect models, applying an intention to treat procedure.

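### The recruitment target of 323 adds 10% to 294 instead of dividing by 0.90, so 10% attrition would leave about 291 adolescents with observed outcomes; the consequence is minor

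*Protocol article*

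**What the plan says.** The Power calculation section describes a calculation for differences among the three conditions, "taking into account two repeated measurements with an assumed correlation of 0.6", with "power = 0.80, alpha = 0.05". It arrives at a required total "of 294 children to obtain an effect size (ES) of 0.40". The attrition step follows: "With an assumed attrition of 10%, we need to recruit 323 participants". The abstract, under Methods/design, gives the same target: "we aim to recruit 323 adolescents (12-16 years".

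The inflation formula is not written out. The article gives no other attrition rate and no other reason for 323. On incomplete data, the Data analytical plan says: "Missing data will be handled by multiple imputations", within an intention-to-treat procedure.

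**The concern.** Three figures stand together in one short paragraph: 294 required, 10% attrition, 323 to recruit. They cannot all hold. If 10% of the recruits are lost, the number to recruit is the required number divided by the retained fraction, 0.90. Adding 10% to the required number takes the percentage of the wrong base and always falls short.

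What is at stake is limited. 323 is the published sample size, and any reader can check it from that paragraph. The section presents 294 as what 0.80 power needs and builds in no visible margin. A target that does not deliver 294 under the article's own attrition assumption therefore leaves the stated power slightly unmet.

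**Working it through.** **Inputs, all from the Power calculation section unless noted**
- Required total before attrition: 294
- Assumed attrition: 10%
- Stated recruitment target: 323 (also in the abstract)
- Effect size 0.40, power 0.80, alpha 0.05. Sidedness is not stated; two-sided is assumed here.
- Three conditions. Equal allocation is inferred from the randomization lists, "comprising lists of six possibilities (2 CHILLED × 2 VAAG × 2 WLCs) at each school", which gives 294 / 3 = 98 per condition.

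**Step 1. Reproduce the stated target.** 294 × (1 + 0.10) = 323.4, which rounds to the stated 323. (Rounded up, as is usual for a sample size, the same method would give 324.)

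**Step 2. Inflate for a 10% loss among recruits.** 294 / (1 − 0.10) = 326.67, rounded up to 327. The gap is 327 − 323 = 4 recruits, or 4 / 327 = 1.2%.

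**Step 3. Check what each target leaves.**

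| Recruited | Left after 10% attrition | Against 294 |
|---|---|---|
| 323 | 323 × 0.90 = 290.7 | 3.3 below |
| 327 | 327 × 0.90 = 294.3 | met |

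**Step 4. Find the attrition that 323 can bear.** 1 − 294/323 = 0.0898, about 9.0%.

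**Step 5. Size the effect on power.** A simple approximation compares two arms on one measurement: power = Φ(0.40 × √(n/2) − 1.96), with n per arm.
- n = 98: Φ(0.40 × 7.000 − 1.96) = Φ(0.840) = 0.800
- n = 290.7 / 3 = 96.9: Φ(0.40 × 6.961 − 1.96) = Φ(0.824) = 0.795

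The loss is about half a percentage point, before any design effect.

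**Step 6. See whether that size depends on the approximation.** The article does not name the test or the pattern of means behind 294. Two routes come close to it:
- The two-arm formula needs 2 × ((1.96 + 0.84)/0.40)² ≈ 98.1 per arm, or 294.3 in total without rounding. It ignores the correlation.
- A three-group omnibus F test with standardized means 0, 0.20 and 0.40, and a variance factor 2 × (1 − 0.6) = 0.8, reaches 0.80 first at 98 per arm, exactly 294 (power 0.803). At 96.9 per arm the same test has power 0.798.

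Both routes put the expected power just under 0.80, with a loss of about half a percentage point. The base figure of 294 is therefore not in dispute; the fault lies in the attrition step alone.

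**The case against.** Four points can be made in defence of 323.

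**The analysis is by intention to treat with multiple imputation.** A reader might infer from the arithmetic that only about 291 adolescents would be analysed. The article does not support that. Under the Data analytical plan everyone randomized is analysed, and the Assessment section plans to collect outcomes whether or not the adolescent stays in the intervention. This part of the objection stands: about 291 is the number with observed outcomes at a time point that suffers the assumed attrition. It does not rescue 323, because imputation does not restore the information in outcomes never observed, and the article itself adds an allowance so that 294 remain after losses.

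**The 0.795 is not the article's own calculation.** This also stands. The formula uses neither the three conditions nor the correlation of 0.6, so the figure shows the order of magnitude only. A reader should not take it as the trial's power on its own stated basis.

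**The shortfall is too small to matter.** Largely true. The 10% is a round assumption, and at 9% attrition 323 suffices. Randomization is by whole groups of 5-8, so the final total moves in steps larger than 4. No design choice or analysis turns on the difference. The figures in the paragraph still contradict one another.

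**Reaching 327 is not free.** A reader might infer that the last group could simply absorb four more adolescents. The Trial status section reports 310 included by November 2016, with inclusion closing in December 2016. Reaching 323 takes 13 more, which two groups (10 to 16 adolescents) can supply. Reaching 327 takes 17 more, beyond two groups of at most 8, so a third would be needed. Nothing in the article shows that one was available.

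**Conclusion.** The point holds as a minor arithmetic error. On the article's own figures, 294 with 10% attrition requires 327 recruits. The stated 323 fits the required number multiplied by 1.10, and under the assumed attrition it leaves about 291 adolescents with observed outcome data, about 3 short. The attrition arithmetic needs nothing beyond the three stated figures. That multiplication was the route to 323 is inferred from the match, since the formula is not shown.

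The power figure rests on more: a two-sided 5% test, equal arms, effect size 0.40 and a two-arm single-measurement approximation that ignores grouping. On that basis power goes from 0.80 to roughly 0.795. A stronger reading, that the trial is materially underpowered by this slip, is not supported: the gap is 1.2% of the target and disappears if attrition is 9% instead of 10%.

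**What to change.** In the Power calculation section, state that 294 with 10% attrition corresponds to 327 recruits. Then take one of two courses.

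1. **Preferred, given how late recruitment is:** keep 323 and add what is expected from it: about 291 adolescents with observed outcomes at 10% attrition and power marginally below 0.80, or 294 with observed outcomes if attrition does not exceed 9%. If a power figure is quoted, name its basis and say that it is before any design effect. This costs one or two sentences and needs no further recruitment.
2. **If the final groups allow it:** change the target to 327 in both the Power calculation section and the abstract. The text change is trivial. The practical cost, counting from 310, is probably a third further group where two could reach 323.

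Under either course, describe the shortfall as one of observed outcomes, since the planned analysis includes everyone randomized.
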